### Study objectives

The primary aim of this study is to compare the Constant score, reflecting functional outcome and pain, after primary hemiarthroplasty (HA) versus non-operative treatment in patients over 65 years of age who sustained a comminuted fracture of the proximal humerus.

Secondary aims are to determine the effect of primary HA versus non-operative treatment on the degree of disabilities of the arm, shoulder and hand (DASH score), level of pain (VAS), the rate of secondary interventions, complications and mortality, the radiographic healing, and the health-related quality of life (Short-Form 36, SF-36, and EuroQol-5D, EQ-5D) in these patients. Finally, upon calculation of the costs for both the HA and the non-operative groups, the cost-effectiveness of these treatments will be determined and compared.

Based upon limited literature data available, our main study hypothesis is that HA will result in higher Constant scores (reflecting better functional outcome with less pain) at 1 year compared with non-operative treatment of comminuted proximal humeral fractures in the elderly Despite higher initial costs, it is expected that HA will be more cost-effective than conservative treatment.

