### Outcome measures

The primary outcome measure will be the Constant score. This scoring system consists of four variables, reflecting both function and pain of the shoulder joint [22]. The subjective variables are pain (15 points), activities of daily living (ADL; i.e., sleep, work, recreation/sport; 10 points), and arm positioning (10 points), which give a total of 35 points. The objective variables are range of motion (ROM; 40 points) and strength (25 points), which give a total of 65 points. ROM includes forward flexion (10 points), lateral elevation (10 points), external rotation related to the head (10 points) and internal rotation related to the spine column (10 points). Forward flexion and lateral elevation are measured using a goniometer. Strength of abduction will be measured using a calibrated spring balance. The right and left shoulders will be assessed separately.

Secondary outcome measures are:

- Disabilities of the Arm, Shoulder and Hand (DASH) score

- Visual Analogue Scale (VAS) for pain

- Rates of secondary interventions

- Radiographic healing

- Mortality rate

- Complication rates

- Health-related quality of life: Short Form-36 (SF-36)

- Health Utility: EuroQol-5D (EQ-5D)

- Healthcare consumption (for cost calculations)

- Cost-effectiveness

The Disabilities of the Arm, Shoulder and Hand (DASH) Outcome Measure is a validated 30-item, self-report questionnaire designed to help describe the disability experienced by people with upper-limb disorders and also to monitor changes in symptoms and function over time [23-25]. The DASH outcome measure is scored in two components: the disability/symptom section (30 items, scored 1-5) and the optional high performance Sport/Music module (4 items, scored 1-5). The DASH disability/symptom score is a summation of the responses to 30 questions on a scale of 1 to 5. Scores may range from 0 points (no disability) to 100 points (severe disability). The questions test the degree of difficulty in performing a variety of physical activities because of arm, shoulder, or hand problems (21 items). They also investigate the severity of pain, activity-related pain, tingling, weakness, and stiffness (5 items), as well as the effect of the upper limb problem on social activities, work, sleep, and self-image (4 items).

Pain level will be determined using a 10-point Visual Analog Scale, in which 0 implies no pain and 10 implies the worst imaginable pain.

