The EuroQol (EQ-5D) is a validated and extensively used general health questionnaire to measure quality of life [27,28]. It is recommended for the assessment of QoL in trauma patients, especially for economic assessments [29,30]. EQ-5D has been developed by the EuroQoL Group in order to provide a simple, generic measure of health for clinical and economic appraisal [31]. EQ-5D consists of the EQ-5D descriptive system and the EQ Visual Analog Scale (EQ VAS). The EQ-5D descriptive system comprises five dimensions: mobility, self-care, usual activities, pain/discomfort, and anxiety/depression. Each dimension is marked as either no problems, some problems, or severe problems, which results in a 1-digit number expressing the level selected for that dimension. The digits for five dimensions are combined in a 5-digit number describing the respondent's health state. The EQ VAS records the respondent's self-rated health on a vertical, visual analog scale. Scores ranging from 0 ('Worst imaginable health state') to 10 ('Best imaginable health state') can be used as a quantitative measure of health outcome as judged by the individual respondents.

Cost measurement will be in accordance with Dutch guidelines for economic evaluations. Healthcare consumption data will be collected using a custom-made questionnaire. Health care costs will include costs of general practice care, medical specialist care, physical therapy, hospitalization, medication, home care, and other costs directly associated with diagnosis, treatment and rehabilitation. Where possible standard cost prices will be used as published by Oostenbrink will be used [32]. In accordance with guidelines for differential discounting, effects will be discounted at a rate of 1.5% and costs at 4% per year [33]. Results will be presented with 95% confidence intervals.

The incremental cost-effectiveness ratio of HA versus conservative treatment will be expressed in a cost-utility ratio, i.e., in terms of cost per Quality-Adjusted Life Years (QALY). Cost-utility ratios will be calculated by dividing the difference in mean costs of the two interventions by the difference in their mean effects. Policy makers and healthcare economists have proposed that costs varying from € 25,000 up to € 75,000 (US$ 31,600 - US$ 94,700) per QALY may be considered as acceptable [34,35].

In addition to the outcome variables mentioned above, the following data will be collected:

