### Statistical analysis

The research data will be reported following the CONsolidated Standards of Reporting Trial (CONSORT). Data will be analyzed using the Statistical Package for the Social Sciences (SPSS) version 16.0 or higher (SPSS, Chicago, Ill., USA). Normality of continuous data will be tested with the Shapiro Wilk test, and homogeneity of variances will be tested using the Levene's test. Protocol violations will be recorded; data will be analyzed with and without patients with protocol violation.

Differences in baseline characteristics (i.e., intrinsic and injury-related variables) between both intervention groups will be assessed using the Student's T-test (parametric numeric data), Mann-Whitney U-test (non-parametric numeric data) or Chi-square test (categorical data). Data will be presented as mean ± SD (parametric data) or medians and percentiles (non-parametric data).

Univariate analysis will be performed to test the difference in primary and secondary outcome measures between the intervention groups using the Student's T-test (parametric data), Mann Whitney U-test (non-parametric data) or Chi-square analysis (categorical data).

Multinomial logistic regression analysis will be performed to model the relation between different covariates and the Constant score. Intrinsic and fracture-related variables that display a p-value < 0.5 in univariate analyses will be added as covariate. Similar models will be made to model the relation between covariates and the other outcome measures.

A p-value < 0.05 (2-sided tests) will be taken as threshold of statistical significance.

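### The normality rule would compare skewed costs by ranks, although the cost-utility ratio rests on mean costs

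*Protocol article*

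**What the plan says.** Three parts of the protocol article bear on this.

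- **Statistical analysis.** "Normality of continuous data will be tested with the Shapiro Wilk test". The arms are then compared "using the Student's T-test (parametric data), Mann Whitney U-test (non-parametric data) or Chi-square analysis (categorical data"). This rule is given for the primary outcome and for every secondary outcome alike. The section makes no exception for any secondary outcome and does not mention costs or QALYs. Its paragraph on baseline characteristics adds: "Data will be presented as mean ± SD (parametric data) or medians and percentiles (non-parametric data").
- **Outcome measures, list of secondary outcomes.** The list includes "Healthcare consumption (for cost calculations") and, as a separate item, cost-effectiveness. Study objectives adds that "upon calculation of the costs for both the HA and the non-operative groups, the cost-effectiveness of these treatments will be determined and compared".
- **Outcome measures, cost measurement.** The paragraph on costing and discounting ends: "Results will be presented with 95% confidence intervals". The next paragraph defines the cost-utility ratio by "dividing the difference in mean costs of the two interventions by the difference in their mean effects" and quotes a range of EUR 25,000 to EUR 75,000 per QALY as possibly acceptable. No method for the intervals is named.

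**The concern.** The Mann-Whitney test compares ranks. It speaks to a difference in means only if the two distributions have the same shape and differ by a shift. The cost-utility ratio needs the difference in arithmetic means, because that is what determines total spending.

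The design makes unequal shapes plausible. The Discussion expects higher initial costs in the hemiarthroplasty (HA) arm because of surgery, so operated patients share a common cost. The Outcome measures section allows later arthroplasty or plate fixation in the conservative arm, so that arm may combine many low costs with a few high ones. The sponsor also expects the higher initial cost of HA to be worthwhile and suggests that less care may be needed later. Similar mean costs with different medians is therefore a case the trial should be able to describe correctly.

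At stake is the cost comparison. A report could state that costs differ significantly when the mean cost per patient is the same, or that they do not differ when the means are far apart, next to a ratio built on means.

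**Working it through.** **Inputs from the protocol article.** Two-sided alpha 0.05; 30 evaluable and 40 randomized patients per group. The 30 reproduces closely: 2 × (1.96 + 0.84)² × 12² / 9² = 27.9, so 28 per group, or 29 with the exact t-test. It serves here only to set the number per arm. The article states no cost figure, so every cost input below is an assumption and a range is shown.

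**Rule simulated.** Shapiro-Wilk p < 0.05 in either arm leads to Mann-Whitney; otherwise Student's t-test. With these skewed costs Shapiro-Wilk rejected in 98% to 100% of trials, so the rule almost always became Mann-Whitney.

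**A case that can be checked by hand.** Take log-normal costs with equal means and log-SD 0.5 (HA) and 1.0 (conservative).

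1. Equal means imply a difference in log-means of (1.0² − 0.5²)/2 = 0.375.
2. The SD of the difference between two log-costs is √(0.25 + 1.00) = 1.118.
3. The probability that an HA patient costs more than a conservative patient is Φ(0.375/1.118) = Φ(0.335) = 0.631, not 0.5, although the means are equal.
4. At 30 per arm the null standard error of this probability is √(61/(12 × 900)) = 0.0752. The power to detect 0.131 is about Φ(0.131/0.0752 − 1.96) = 42%.
5. At 40 per arm the standard error is √(81/(12 × 1,600)) = 0.0650, and the power is about 52%.

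Simulation of the full rule gave 41% and 52%, against 8% for Welch's t-test.

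**Conversion scenario, equal true means.** Conservative costs are log-normal with median EUR 3,000 and log-SD 0.5, so the mean is 3,000 × exp(0.125) = 3,399. A further 15% of these patients incur an add-on. HA costs are log-normal with the same overall mean.

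| Assumed mean add-on (EUR) | Common mean: 3,399 + 0.15 × add-on | Rule rejects, 30 per arm |
|---|---|---|
| 5,250 | 4,187 | 18% |
| 10,000 | 4,899 | 48% |
| 15,000 | 5,649 | 76% |
| 35,000 | 8,649 | 99% |

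Welch's test rejected in about 6% to 12% across these rows.

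**Other assumed shapes** (20,000 trials each, 4,000 for the two-stage rule; equal means of about 10,000 except in the last row).

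| Scenario | Rule, 30 / 40 per arm | Welch, 30 / 40 per arm |
|---|---|---|
| Same shape, log-SD 0.8 in both | 4.6% / 4.7% | 4.3% / 4.6% |
| Log-SD 0.4 vs 0.8 | 29% / 36% | 7% / 7% |
| Log-SD 0.3 vs 1.2 | 80% / 89% | 14% / 13% |
| Fixed cost 7,000 plus small skewed cost vs skewed cost | 64% / 76% | 11% / 10% |
| 15% with a flat add-on of 20,000, base mean 7,000 | 23% / 29% | 6% / 6% |
| Equal medians 8,000, means about 8,700 vs 13,200 | 6% / 6% | 22% / 35% |

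The last row is the reverse error: the rule hardly reacts to a real difference in means of about 4,500.

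**The case against.** The strongest reply is that the economic evaluation has its own text. The cost measurement paragraphs set out unit prices, discounting, a difference in means and 95% confidence intervals, while the Statistical analysis section never mentions costs. On that reading the normality rule is for clinical outcomes, and a rank test on resource use is not an error in itself. This is a fair reading, and it is why the point is minor. It does not remove the point, because the rule is stated for all secondary outcomes, healthcare consumption is one of them, and nothing says which text prevails.

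A second reply is that the high rejection rates need strong assumptions. This stands. In the conversion scenario, equal means require each conversion to cost 1/0.15 = 6.7 times the extra cost of an HA patient. If the HA excess is EUR 5,250 and a conversion costs once or twice that, HA is truly dearer by 5,250 − 0.15 × 5,250 = EUR 4,463, or by 5,250 − 0.15 × 10,500 = EUR 3,675. At 30 per arm Mann-Whitney then rejects in over 99% of trials and Welch in 99.8% or 84%, both rightly. The 99% for equal means is one end of a range, not an expected rate.

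A reader might go further in three ways that the document does not support:

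- That cost-effectiveness could not be judged at the quoted thresholds. The ratio already uses means, and the choice of test does not change it.
- That a confidence interval will be placed on the ratio. The sentence promising intervals closes the costing paragraph, before the ratio is introduced, and does not say so.
- That the lack of a bootstrap method or an acceptability curve is itself a fault. An article may leave such detail to the full protocol or analysis plan, neither of which is shown.

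**Conclusion.** The point holds as a mismatch between two stated rules. As written, skewed costs fall under a rank test, while the economic result is defined on means, so the cost p-value and the ratio can answer different questions. In the equal-mean conversion scenarios the rule rejects in roughly 18% to 99% of trials at 30 per arm, against about 6% to 12% for a test of means. Across the other unequal shapes with equal means shown it was 23% to 80%, with tests of means at about 6% to 14%. If both arms have the same shape there is no false signal.

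These sizes rest wholly on assumed cost distributions and on reading the blanket rule literally; the article never says outright that costs will be tested by Mann-Whitney. Tests of means are themselves somewhat above 5% under strong skew. Severity is minor: only a secondary outcome is affected, and neither the Constant score analysis nor the ratio is touched.

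**What to change.** Add to the Statistical analysis section, or to the analysis plan:

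- Costs and QALYs are exempt from the normality rule. They are summarized and compared as arithmetic means whatever their distribution.
- The differences in mean cost and mean QALYs are given with non-parametric bootstrap 95% confidence intervals, resampling each patient's cost and QALY as a pair within arm.
- If uncertainty in cost-effectiveness is reported, give the incremental net monetary benefit (threshold × difference in mean QALYs − difference in mean costs) with its 95% confidence interval at EUR 25,000 and EUR 75,000 per QALY, rather than an interval on the ratio.

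Medians and percentiles of cost may still be shown as description. The change costs a few lines of wording and a short bootstrap script. It needs no extra data or patients and leaves the primary analysis unchanged.

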### Sample size calculation

Calculation of the required sample size is based on the assumption that the mean Constant score will be 47 in the conservatively treated patients and 56 in the HA group, assuming a SD of 12 for each group [10,14].

A two-sided test with an alpha level of 0.05 and a beta level of 0.2 requires 30 patients in every group. Anticipating a mortality rate of 10% in the first year due to a natural death rate in elderly patients [36], and a conservative dropout rate of 20% loss-to-follow up (based upon experience in previous trials), projects to a required sample size of 40 per group.

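### The multivariable model named for the Constant score, multinomial logistic regression, does not suit a 0-100 numeric score and gives no usable adjusted estimate; its p < 0.5 covariate screen also needs replacing

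*Protocol article*

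**What the plan says.** Under Outcome measures the Protocol article says that "The primary outcome measure will be the Constant score". It builds the score from subjective items, "which give a total of 35 points", and objective items, "which give a total of 65 points", so the scale runs from 0 to 100. The Sample size calculation treats it as a numeric quantity: it assumes that "the mean Constant score will be 47 in the conservatively treated patients and 56 in the HA group", with a common standard deviation of 12.

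The Statistical analysis section first compares the groups on primary and secondary outcomes by t-test, Mann-Whitney U test or chi-square test, according to the type of data. It then turns to multivariable work: "Multinomial logistic regression analysis will be performed to model the relation between different covariates and the Constant score". The selection rule follows: "Intrinsic and fracture-related variables that display a p-value < 0.5 in univariate analyses will be added as covariate". The approach is carried further: "Similar models will be made to model the relation between covariates and the other outcome measures". No categories or cut-points of the Constant score appear anywhere in the article, and treatment group is not named as a term in the model. The Abstract announces univariate and multivariable analyses on an intention-to-treat basis.

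**The concern.** Multinomial logistic regression models the probability of each of several unordered categories, with a separate set of coefficients for every category but one. Applied to a numeric total it ignores order and distance, and it has no parameter that is a difference in points. The model named therefore does not fit the outcome as the article itself defines it and sizes the trial on it.

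This is the only multivariable model type that the article names. In a trial of 80 patients some chance imbalance at baseline is to be expected, and the Background criticises the earlier randomised trial for a difference in age at baseline. Readers will want an adjusted result. As the text stands, the analyst would have to depart from the published plan and settle the model, any categories and the covariates after the data are in.

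The covariate rule adds a second difficulty. Selection at p < 0.5 in the trial's own data screens out very little and leaves the covariate list unknown until the outcome data are seen.

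**Working it through.** **Inputs.** Means 47 and 56, SD 12, two-sided alpha 0.05, power 80%, 30 evaluable and 40 randomised per group, 10% mortality and 20% loss to follow-up (all from Sample size calculation); scale 35 + 65 = 100 (Outcome measures); candidate covariates from the lists of intrinsic and injury-related variables at the end of Outcome measures. Assumed here: scores are normal and recorded as whole numbers.

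**1. The plan's own figure.** n = 2 × (1.96 + 0.84)² × 12² / 9² = 27.9, so 28 per group by the normal approximation; the exact t calculation gives 29 (power 80.1%). The stated 30 gives 81.5%. The sample size for a difference in means is reproduced. Evaluable patients: 2 × 30 = 60 by the plan's figure, or 80 × (1 − 0.10 − 0.20) = 56 if both allowances are used in full.

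**2. Outcome levels.** In simulated trials at the planning values, the number of distinct scores averages 33.4 among 56 patients and about 35 among 60 (95% range 30-40). At 60 patients about 19 scores occur in one patient only.

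**3. Parameters.** With K levels and p predictors the model has (K − 1) × (p + 1) parameters.
- K = 33, treatment only: 32 × 2 = 64, against 56 patients.
- K = 35, treatment only: 34 × 2 = 68, against 60 patients.
- K = 35, treatment plus 3 covariates: 34 × 5 = 170.
- K = 35, treatment plus 6 covariates: 34 × 8 = 272.

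A score seen in one patient is seen in one arm only, so its treatment coefficient against a level seen in both arms has no finite estimate.

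**4. What a fit returns.** In one simulated data set of 60 patients (K = 35):
- Treatment only: coefficients up to 46 in absolute value and no invertible Hessian, hence no standard errors.
- Treatment plus 3 covariates: no convergence, standard errors up to about 66,000.
- Treatment plus 6 covariates: no convergence and an undefined log-likelihood.

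Linear regression on the same data gave a treatment difference with a standard error of about 3.1-3.2 points in all three cases. The planning value is 12 × √(2/30) = 3.1.

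**5. The screening rule.** The lists contain 8 intrinsic and 3 injury-related entries, 11 in all, or up to 13 if combined entries are split. A variable unrelated to the outcome passes p < 0.5 about half the time: 0.5 × 11 = 5.5 and 0.5 × 13 = 6.5. At p < 0.05 the figures would be 0.55 and 0.65.

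**6. What the screen does in a linear model.** Simulation with 13 candidates screened against the outcome at p < 0.5, followed by a linear model with treatment (28 or 30 per arm, 5,000 trials per setting): type I error 4.6-5.3%, coverage of the 95% interval 94.2-95.4%. With pure-noise candidates and a true difference of 9 points, power at 28 per arm falls from about 79% to about 69%.

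**The case against.** Several points on the other side stand.

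- The between-group test of the primary outcome is the t-test or Mann-Whitney test, which the multinomial sentence does not touch. A reader might infer that the primary comparison is invalid or the trial missized. The article does not support that: the t-test matches the basis of the sample size.
- The sentence speaks of covariates and does not name treatment. Calling it the adjusted treatment comparison is an inference from the Abstract's mention of multivariable analyses. If it is only a prognostic model, it still does not suit the outcome.
- A reader might infer that the score will be cut into bands and charge the trial with the power lost. No bands are planned anywhere, so no such loss can be attributed to it.
- A reader might also infer that screening at p < 0.5 makes the treatment effect's p-value and confidence interval unreliable. Step 6 does not bear this out; the cost found is in power. The 0.5 may also be a misprint, which the article cannot settle.
- The wording on similar models need not mean the multinomial type for every outcome. Several secondary outcomes (secondary interventions, healing, mortality, complications) are categorical in any case.
- Software may accept each score as a category, so the fair statement is that there is no usable fit, not that no program will run.

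An unseen analysis plan might correct the model. It would not change the article, which positively names an unsuitable one.

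**Conclusion.** Wrong as written, and confined to the multivariable analysis. The article assigns a model for unordered categories to a 0-100 numeric score and gives no categories. Parameters exceed patients even with treatment as the only predictor, and no adjusted mean difference results. If similar models means the same type, the fault extends to the other numeric outcomes: DASH, VAS pain, the SF-36 scales, EQ-5D utility and EQ VAS.

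The p < 0.5 rule is close to unselective. Its price in a linear model is about 10 percentage points of power at 28 per arm when the candidates are noise, without material harm to type I error or coverage.

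The level and parameter counts assume normal, whole-number scores at the planning values. The power figure assumes 13 candidates and screening against the outcome.

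**What to change.** - Replace the multinomial model with linear regression (ANCOVA) of the 12-month Constant score on treatment and a short prespecified list of baseline covariates, for example age, sex and a pooled fracture category. Report the adjusted mean difference with its 95% CI. The fracture classes must be pooled: the eligibility criteria admit Hertel types 2, 9, 10, 11 and 12 and split-head fractures, six categories and so five coefficients if left apart.
- Delete the univariate p < 0.5 screen.
- State the model type for each other outcome, with linear models for the numeric ones.
- Leave binary outcomes with few events unadjusted or minimally adjusted. At the assumed 10% mortality there would be about 0.10 × 80 = 8 deaths, too few for a multi-covariate logistic model.

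The cost is wording and minor analysis work. The listed covariates are already collected, and N stays at 40 per group.

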**Methods/Design:**

A prospective, multi-center RCT will be conducted in nine centers in the Netherlands and Belgium. Eighty patients over 65 years of age, who have sustained a three-or four part, or split head proximal humeral fracture will be randomized between primary hemiarthroplasty and conservative treatment. The primary outcome is the Constant score, which indicates pain and function. Secondary outcomes include the Disability of the Arm and Shoulder (DASH) score, Visual Analogue Scale (VAS) for pain, radiographic healing, health-related quality of life (Short-form-36, EuroQol-5D) and healthcare consumption. Cost-effectiveness ratios will be determined for both trial arms. Outcome will be monitored at regular intervals over the subsequent 24 months (1, 3 and 6 weeks, and 3, 6, 12, 18, and 24 months). Data will be analyzed on an intention to treat basis, using univariate and multivariable analyses.

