a) Intrinsic variables (baseline data): dominant side, age, gender, American Society of Anesthesiologists (ASA) grade, alcohol and tobacco consumption, comorbidity including osteoporosis, household composition, and medication use

b) Injury related variables: affected side, mechanism of injury, fracture classification (Hertel)

c) Intervention-related variables: surgical delay (i.e., time between fracture and surgery; HA-group only), time between injury and start of physical therapy, days of collar and cuff use, and total number of physical therapy sessions

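### The p < 0.5 covariate-entry models are extended to mortality, where the protocol's own figure of about 8 first-year deaths leaves roughly one event per model parameter

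*Protocol article*

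**What the plan says.** The Statistical analysis section of the Protocol article describes a regression of the Constant score on covariates. Every intrinsic or fracture-related variable with a univariate p-value below 0.5 enters. The next sentence carries this over without exception: "Similar models will be made to model the relation between covariates and the other outcome measures".

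The Outcome measures section lists the other outcomes. Beside the continuous scales they include mortality, complication rates and "Rates of secondary interventions". The same section gives the candidates, beginning "Intrinsic variables (baseline data): dominant side, age, gender", followed by the injury-related variables.

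The trial plans "Eighty patients over 65 years of age", and the Sample size calculation section is explicit about deaths: "Anticipating a mortality rate of 10% in the first year". It gives no two-year mortality figure and, like the rest of the article, no expected rate for complications or secondary interventions. A separate paragraph of the Statistical analysis section already plans an unadjusted chi-square comparison of the arms for categorical outcomes.

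**The concern.** A threshold of 0.5 removes only about half of the variables that have no relation to the outcome. For a continuous score in some 60 to 80 patients that costs precision. For a binary outcome the information lies in the rarer category, and here that may be a handful of deaths. Once the number of coefficients approaches the number of events, some combination of covariates often separates deaths from survivors perfectly. The maximum-likelihood fit then has no finite solution, and software may still print very large odds ratios. Even finite estimates are overfitted.

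Replacing the model for the Constant score would not cure this. A logistic model is the natural family for death; there are simply too few deaths for the number of covariates that the rule lets in. Mortality is among the harms to be set against any functional gain from surgery, so unstable covariate results for it should not be built into the plan.

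**Working it through.** **The plan's own sample size.** For a difference of 56 − 47 = 9, SD 12, two-sided alpha 0.05 and 80% power, the normal approximation gives 28 per group and the t-test 28.9, so 29. The stated 30 is reproduced within two patients. The stated 40 per group equals 28/(1 − 0.30), and is within two of 30/(0.9 × 0.8) = 41.7. The total of 80 is used below.

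**Events.** First-year deaths: 0.10 × 80 = 8. If the 20% loss to follow-up is unrelated to death, about 8 × 0.8 = 6.4 would be observed. Follow-up lasts two years. Assuming a constant hazard, which the article does not state, two-year deaths are 80 × (1 − 0.9²) = 15.2.

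**Parameters.** There are 9 intrinsic candidates, counting alcohol and tobacco separately, and 3 injury-related ones: 12 in all. Under no association about 12 × 0.5 = 6 enter. At one degree of freedom each that is 6 parameters, or 7 if arm is added. If ASA grade, household composition and Hertel type keep several levels, the count is about 10.

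**Events per parameter.**
- 8 deaths: 8/6 = 1.3, 8/7 = 1.1, 8/10 = 0.8.
- 15 deaths (assumed): 15/6 = 2.5, 15/10 = 1.5.
- Any binary outcome: the rarer category cannot exceed 40 of 80, so at best 40/7 = 5.7 and 40/10 = 4.

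**Simulation of the stated rule.** The set-up was 80 patients, 12 candidates, the p < 0.5 screen, a binary logistic model with arm included, and 500 runs per setting. Linear programming detected the absence of a finite fit. Ranges cover screening against outcome or against arm, with and without true covariate effects. Covariate prevalences and category counts are assumptions.

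| Event rate | Coding | Parameters | Median events per parameter | No finite fit |
|---|---|---|---|---|
| 10% (about 8) | 1 df each | 7.1-7.8 | 1.0-1.1 | 51-69% |
| 10% (about 8) | multi-level | 10.3-10.9 | 0.75-0.80 | 82-92% |
| 19% (about 15) | 1 df each | 7.1-7.8 | 2.0-2.1 | 21-32% |
| 19% (about 15) | multi-level | 10.4-10.9 | 1.4-1.45 | 56-70% |
| 30% (about 24) | 1 df each | 7.1-7.9 | 3.0-3.4 | 7-15% |
| 30% (about 24) | multi-level | 10.2-11.1 | 2.1-2.3 | 26-42% |

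A further simulation at about 8 deaths gave 45-75% whether or not arm was in the model. A run with fewer sparse covariates, in which a fit failed if a coefficient could not be estimated, gave 9-16%. The 30% row is illustrative only.

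**The case against.** Several counter-arguments carry weight.

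- *The comparison of arms is not at stake.* A reader might infer that the plan will report unstable adjusted treatment effects on safety. The article does not support that. It describes these models as relating covariates to outcomes, never says that arm is included, and tests the arms separately by chi-square. Even with arm forced in at a 10% event rate, the arm coefficient itself failed in only 5-13% of simulated fits; the high percentages count any failed coefficient. This stands.
- *Eight deaths say nothing about the other event outcomes.* A reader might infer that complication and re-intervention models will also often fail. With no stated rate for either, that cannot be derived. Only the ceiling of about 4 to 6 events per parameter applies to them. This stands.
- *Eight is a first-year figure.* True, but about 15 deaths over two years would still be too few.
- *The size depends on assumed prevalences.* True of the simulated percentages. The events-per-parameter ratio does not depend on prevalences, only on how many levels each variable keeps.
- *The entry rule is the real cause.* Largely so: with an illustrative p < 0.05 screen, models had 1.5-1.8 parameters and any-coefficient failure at 8 events fell to 14-20%. But the extension to mortality is what turns a loose screen into models that may have no solution.
- *Sparse-event methods belong in a fuller document.* Their absence is not the point. The article states a rule and its scope, and following that rule as written leads to the problem.

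**Conclusion.** The point holds for mortality. Applied as written, the rule puts 6 to 10 parameters on about 8 first-year deaths, or 0.8 to 1.3 events per parameter. About 15 deaths over two years, an assumption, would raise this only to 1.5-2.5. At 8 deaths, at least one coefficient lacked a finite estimate in roughly half to most simulated trials (about 45-90%), with 9-16% under one less sparse set of assumptions. These percentages rest on assumed prevalences and category counts and on reading the planned models as binary logistic for death.

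For complications and secondary interventions the supported conclusion is weaker: overfitting is a risk at any event rate, but failure to fit cannot be shown. The unadjusted comparison of arms remains sound in this respect. The matter is worth correcting and does not threaten the primary analysis.

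**What to change.** Limit the sentence on similar models to the continuous outcomes: DASH, VAS, SF-36 and EQ-5D. For mortality, complications and secondary interventions, report the difference between arms with a 95% confidence interval alongside the planned test. If adjustment is wanted and events are few, use at most one covariate named in advance, for example age, with Firth penalised likelihood, and drop the p < 0.5 screen for these outcomes.

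This changes one sentence and adds a short one, with no effect on data collection or sample size. The price is that no multi-covariate model is reported for the binary outcomes.
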